## Abstract

**Background:**

Nearly all individuals with Alzheimer disease and related dementias (ADRD) experience behavioral and psychological symptoms of dementia (BPSD), which include symptoms such as agitation, wandering, delusions, and hallucinations. Care partners (a person, often a family member, who provides care and support to someone with ADRD) struggle to manage BPSD, making symptom management a critical focus of intervention research. Our team has developed a mobile telehealth intervention (Brain CareNotes) to help care partners manage BPSD.

**Objective:**

This paper outlines a protocol for a randomized controlled trial of 160 care partners of patients with ADRD to test the effect of Brain CareNotes on care partner burden and patients’ BPSD.

**Methods:**

Participants will be recruited from partner health systems in Indiana, United States, by word of mouth, and through community outreach efforts. They will be randomly assigned to use either the Brain CareNotes mobile app intervention—which helps care partners manage BPSD through the support of a care coach, written and visual materials on developing care skills, and BPSD measurement and tracking—or an education-only mobile app control for 12 months. Data will be collected over the phone at baseline, 6 months, and 12 months. Primary outcomes assessed for this trial are (1) care partner burden and (2) patients’ BPSD. Secondary and exploratory outcomes assessed include care partner depressive symptoms, patient and care partner acute care use, intervention usability and acceptability, and intervention use. The trial will also collect patient and care partner demographics and measure care partner self-efficacy, care partner social support, patients’ ADRD severity, and patients’ functional abilities.

**Results:**

As of March 2025, we have enrolled 159 participants, and 42 have successfully completed the study.

**Conclusions:**

Brain CareNotes is a unique mobile app intervention to support care partners in managing BPSD. Due to the scalability of mobile health interventions, if Brain CareNotes is shown to be effective in reducing caregiver burden and patients’ BPSD, it has the potential for widespread adoption to support many ADRD care partners.

**International Registered Report Identifier (IRRID):**

DERR1-10.2196/73387

## Introduction

The National Plan to address Alzheimer disease and related dementias (ADRD) identifies behavioral and psychological symptoms of dementia (BPSD) as a critical focus of intervention research [1]. BPSD include both behavioral (eg, agitation, aggression, and wandering) and psychological (eg, delusions and hallucinations) symptoms [1]. Almost everyone with ADRD will experience BPSD, yet care partners (nonprofessional caregivers who are often family members of the person with ADRD) report having unmet needs for support with BPSD [2-5]. BPSD are often poorly managed, increasing the risk of avoidable hospitalizations, morbidity, mortality, and nursing home placement [4,6-12]. Care partners struggle to manage BPSD on their own, especially as conditions and symptoms change, leading to increased care partner stress, depression, and risk of mortality [12-15].

The PREVENT randomized controlled trial (R01HS010884) developed and evaluated a BPSD intervention that included care partner–facing materials and BPSD measures [16]. The intervention significantly reduced care partner burden and patients’ BPSD after 12 months when compared with augmented usual care [16]. The PREVENT intervention was then translated into a self-sustained clinical service called the Aging Brain Care clinic [17-20], which demonstrated the ability to hire, train, and use empathetic, nonclinically trained community health workers as care coaches to assist care partners with BPSD management. The Aging Brain Care clinic has had positive effects on BPSD and caregiver burden outcomes [18], but there are barriers to implementing a clinic-based intervention at scale (eg, reliance on in-person encounters, limited clinic operating hours, and the need to employ local clinicians) [17-22].

The National Institute on Aging’s published priorities call for technological interventions for ADRD care [23]. Remote technology (hereafter referred to as telehealth) solutions are especially desired because they can substitute for or extend clinic-based programs, which are costly, hard to scale, and hampered by rising staffing shortages [24]. With record rates of telehealth and mobile app use, now is the time to rigorously investigate technology-based remote interventions for managing BPSD.

Our team developed Brain CareNotes, which distills the Aging Brain Care Model [16,17] into a secure mobile telehealth app for care partners to manage BPSD with the aid of a remote care coach. It was professionally developed in collaboration with care partners, clinical staff, and leaders in the Aging Brain Care clinic but designed for scalability and broad use across settings. To our knowledge, Brain CareNotes is the first app of its kind [25] and delivers remote care support, BPSD measurement and tracking, psychoeducation, and person-centered care planning. Brain CareNotes was pilot tested with 53 care partners of patients with ADRD [26,27] and was demonstrated to be usable and acceptable by care partners. Although not statistically significant, the pilot test also indicated that Brain CareNotes may be effective in reducing care partner burden and patients’ BPSD.

The aim of this study is to test the effectiveness of Brain CareNotes in a larger-scale, randomized, parallel group clinical trial. Figure 1 depicts the study’s conceptual model (shaded sections are investigated in the current trial) based on the best-practice models of ADRD care [28,29]. Like PREVENT and the Aging Brain Care clinic, we anticipate that Brain CareNotes will decrease care partner burden and patients’ BPSD (study primary outcomes), while also lowering care partner depressive symptoms (study secondary outcome). It is hypothesized that improvements in these outcomes will also decrease the acute care use of both patients with ADRD and their care partners (secondary outcome). Care partner self-efficacy and social support are also being measured as the hypothesized primary social-behavioral mechanisms mediating the efficacy of Brain CareNotes [30,31].

**Figure 1 figure1:**
[figure not shown]
I-CARE 2 conceptual model. BPSD: behavioral and psychological symptoms of dementia.

## Methods

### Study Design

This study is a randomized controlled trial of 160 ADRD care partners to evaluate the real-world efficacy of Brain CareNotes on the primary outcomes of care partner burden and patients’ BPSD; patients with ADRD are not enrolled in the study, only their care partners are enrolled. Participants will be recruited from 2 health systems, by word of mouth, and from community outreach efforts and randomized to receive either the Brain CareNotes intervention or an education-only attention control app. Participants will remain in the study for 12 months.

The primary objectives of this trial are to test the effect of Brain CareNotes on (1) care partner burden and (2) patients’ BPSD after 12 months of use. Both primary outcomes will be assessed using the care partner-reported Neuropsychiatric Inventory (NPI) [32,33].

The secondary objectives are to test the effect of Brain CareNotes on (1) care partner depressive symptoms and (2) patient and care partner acute care use at 12 months. For care partner depressive symptoms, we will use the researcher-administered 9-item Patient Health Questionnaire-9 [34,35]. Acute care use data will be obtained from participant self-reports to identify both their and the patients’ hospital and emergency room visits that occurred within 12 months of enrollment.

To measure the predicted social-behavioral mechanisms mediating the efficacy of Brain CareNotes, we will also measure (1) care partner self-efficacy and (2) care partner social support at baseline, 6 months, and 12 months. These are measured using the Revised Scale for Caregiving Self-Efficacy [36] and the Multidimensional Scale of Perceived Social Support (MSPSS) [37], respectively.

App use, acceptability, and usability will also be obtained from participant self-reports at 6 and 12 months. App usability will be assessed using the Simplified System Usability Scale [38], and app acceptability will be assessed using the Behavioral Intention Questionnaire [39-41]. To track participant and patient characteristics, we will collect demographics for both the participant and the patient and assess patient functional abilities and dementia stage by having the participant complete the Functional Activities Questionnaire (FAQ) [42] and the Quick Dementia Rating System (QDRS) [43]. We will also share an app use questionnaire consisting of 2 questions: (1) “Over the last six months, how often have you used the app?” (2) “Over the last six months, when you have accessed the app, how long have been on it?”

Study outcomes are summarized in Table 1.

**Table 1 table1:** I-CARE 2 study outcomes.

Outcome type and domain			Measure
**Primary**			
	Care partner burden	NPI^a^ caregiver distress subscore	
	Patients’ BPSD^b^	NPI	
**Secondary**			
	Care partner depressive symptoms	PHQ-9^c^	
	Care partner and patient acute care use	Self-report hospital and emergency room visits	
**Mechanism**			
	Care partner self-efficacy	Revised Scale for Caregiving Self-Efficacy	
	Care partner social support	MSPSS^d^	
**Process**			
	App use	In-app activity logs (intervention only), app use questionnaire (both groups)	
	App acceptance	Behavioral Intention Questionnaire	
	App usability	Simplified SUS^e^	
**Patient characteristics**			
	Functional abilities	FAQ^f^	
	Dementia stage	QDRS^g^	
	Patient demographics	Participant report	
**Participant characteristics**			
	Care partner demographics	Self-report	

^a^NPI: Neuropsychiatric Inventory.

^b^BPSD: behavioral and psychological symptoms of dementia.

^c^PHQ-9: 9-item Patient Health Questionnaire.

^d^MSPSS: Multidimensional Scale of Perceived Social Support.

^e^SUS: System Usability Scale.

^f^FAQ: Functional Activities Questionnaire.

^g^QDRS: Quick Dementia Rating System.

### Setting and Participants

This study has a planned enrollment of 160 care partners of patients with ADRD. There will be 80 participants in the intervention arm and 80 in the attention control comparator. We will obtain lists of eligible care partners’ contact information from partner health systems in Indiana, United States, including (1) primary care clinics at Indiana University Health (a nonprofit academic health care system), (2) Healthy Aging Transition Services clinics at Community Health Network (a nonprofit health care system), and (3) Eskenazi Health (a public health care system with special emphasis on vulnerable populations in Indiana). Care partners will be identified either by searching patient databases for patients with an ADRD diagnosis (the care partner will be their contact person) or by working with health care professionals at specific clinics to identify potentially eligible care partners. We will also distribute study information at conferences, in communities of interest, and by word of mouth (Multimedia Appendix 1). In addition to these recruitment efforts, our study is listed in databases such as ClinicalTrials.gov and Indiana University’s All IN for Health study listings. These postings reach potential participants statewide, nationwide, and internationally. We will consider international participants on a case-by-case basis and take into account international research ethical standards.

### Sample Size

The sample size was determined to achieve at least 80% power to detect group differences on both primary outcomes: care partner burden and BPSD. Adequate power required 64 participants per group (or N=128 in total) based on previous work [16]. Conservatively estimating 75% retention, a target total of 160 was set.

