### Analyses

At 12 months, the NPI Caregiver Distress scale will be compared between study groups using an analysis of covariance model with fixed effects for Brain CareNotes (vs attention control), health system, age, sex, race, recruitment source, and baseline values for NPI Caregiver Distress and NPI Total Score scales. For between-group comparisons, the difference in least squares means, corresponding SE, 2-sided 95% CIs, and 2-tailed *P* value will be derived from this analysis of covariance model and presented. Within-group change (least squares) means, corresponding SEs, 2-sided 95% CIs, and 2-tailed *P* values will also be presented. Standard model diagnostics will be performed to assess the validity of the proposed model; these diagnostics will include an examination of the residuals for normality, linearity, and homoscedasticity as well as testing for the significance of the intervention by baseline values interaction term to examine if intervention effect differs depending on the baseline levels of NPI Caregiver Distress or NPI Total Score scales.

The NPI Caregiver Distress scale will also be analyzed using a generalized linear mixed model (GLMM) [54,55] with an identity link function. GLMM allows us to analyze longitudinal data at each time point (baseline, 6 months, and 12 months) adjusting for multilevel dependencies within an individual (nested in the study group) and to explore additional covariates as mentioned earlier. Random intercepts, slopes, and fixed covariate effects will be estimated as needed. Time will be modeled as a continuous and categorical variable to model linear and nonlinear changes in care partner burden, respectively. The interaction between study group and time (ie, days between assessments) will be tested to determine if the rate of change in care partner burden is different between study groups. Standard model diagnostics will be performed to assess the validity of proposed models; these diagnostics will include examining the residuals for normality, linearity, and homoscedasticity and testing for the significance interaction term of the intervention by the baseline levels of the NPI Caregiver Distress and NPI Total Score scales. The variance-covariance structure of the random effects will be dependent on the variability among participants within groups. A preliminary test will be conducted to assess the significance of the homogeneity of variances [56] for within-group differences.

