### Limitations and Potential Challenges

There are some limitations and potential challenges to this study. First, while we have had success in recruiting participants on time, there are concerns about retaining participants in the study for the entire 12-month duration. Sample size was calculated assuming a 75% participant retention rate, as the 6-month pilot had 85% of participants complete the study. However, the likelihood of care recipient death or nursing home placement increases with the duration of the study, and this may impact our ability to retain as many participants as previously anticipated. In addition, our team does not have the ability to control the “dosing” of the intervention that participants receive, as they are able to use Brain CareNotes at their own discretion. This means that those randomized to the intervention group likely have differing app use patterns, which could affect its efficacy. While this is reflective of real-world use patterns of commercially available mobile apps, we are attempting to control this by sending app use reminders to participants in both the intervention and control groups every 2 weeks. Currently, Brain CareNotes is a website optimized for mobile viewing, so it is compatible with all mobile devices that can access the internet through a browser. In the future, it could be adapted into an app and made widely available on public app marketplaces (eg, Apple App Store and Google Play Store) for download onto a mobile device. While there are costs associated with Brain CareNotes once built (eg, technology maintenance and security and care coach compensation), it is likely that these costs are lower than other types of interventions. In addition, a mobile telehealth intervention like Brain CareNotes can remove some barriers to care partners (eg, geography) accessing BPSD support.

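### The enrolment target of 160 does not follow from 128 participants at 75% retention: 75% of 160 leaves 60 per arm, 4 below the stated requirement of 64

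*Protocol article*

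**What the plan says.** The Sample Size section of the protocol article makes three statements in sequence.

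- The goal: "The sample size was determined to achieve at least 80% power to detect group differences on both primary outcomes: care partner burden and BPSD".
- The number needed for it: "Adequate power required 64 participants per group (or N=128 in total) based on previous work [16" (the quote stops inside the reference bracket).
- The enrolment target: "Conservatively estimating 75% retention, a target total of 160 was set".

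Setting and Participants confirms equal allocation: "There will be 80 participants in the intervention arm and 80 in the attention control comparator". Limitations and Potential Challenges repeats the retention figure and gives its basis: "Sample size was calculated assuming a 75% participant retention rate, as the 6-month pilot had 85% of participants complete the study".

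The article does not give the effect size, the standard deviation or the alpha used for the calculation. The Analyses section plans a two-sided comparison at 12 months, adjusted for baseline values.

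**The concern.** A required number of completers, a retention rate and an enrolment target are tied together by one division. Here the three stated values do not satisfy it, and the target is too small for the other two. Equal allocation is stated, so unequal arms do not explain the gap, and a difference of 11 or 12 participants is too large for rounding.

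This paragraph is the only support in the article for the power claim. The Results section reports 159 participants enrolled by March 2025, so the size is in effect fixed. If the trial ends with a null result on either primary outcome, readers will judge it against a claimed power of 80% or more, which the plan's own retention assumption does not support as written.

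**Working it through.** **Inputs from the article.** Required analysable number: 64 per group, 128 in total. Retention: 75%. Enrolment target: 160, as 80 per arm.

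**Inputs assumed.** Alpha 0.05 two-sided (the Analyses section reports two-sided 95% intervals, but no design alpha is given). Standardised difference d = 0.50, inferred because 64 per arm is the number a two-sample t test needs at d = 0.50 for 80% power (63.8, rounded up).

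**Step 1: can 160 be reproduced?**

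- Enrolment = completers / retention = 128 / 0.75 = 170.7, so 171. With equal arms, 64 / 0.75 = 85.3, so 86 per arm and 172 in total. The stated 160 is not reproduced; the gap is 11 (or 12).
- Two other routes give exactly 160: 128 x 1.25 = 160 (adding 25% instead of dividing by 0.75) and 128 / 0.80 = 160 (80% retention). The article does not show which was used.

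**Step 2: what 160 yields at 75%.**

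160 x 0.75 = 120, or 60 per arm. Shortfall: 64 - 60 = 4 per arm, 8 in total.

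**Step 3: power at 60 per arm.**

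The noncentrality is d x sqrt(n/2).

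| n per arm | d x sqrt(n/2) at d = 0.50 | Power, t test | Power, normal approximation |
|---|---|---|---|
| 64 | 0.50 x sqrt(32) = 2.83 | 80.1% | 80.7% |
| 60 | 0.50 x sqrt(30) = 2.74 | 77.5% | 78.2% |

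The result does not depend on choosing 0.50. If d is instead solved so that 64 per arm gives exactly 80%, then d = (1.960 + 0.842) x sqrt(2/64) = 0.495, and 60 per arm gives 77.4%.

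**Step 4: sensitivity to the unstated alpha.** With the effect again solved from exactly 80% at 64 per arm, power at 60 per arm is 77.1% for a two-sided alpha of 0.025 and 77.7% for a one-sided alpha of 0.05. The loss stays between 2 and 3 points.

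**Step 5: the retention figure, as a caution only.** The basis given for 75% is 85% completion in a 6-month pilot, and this trial follows participants for 12 months. If the same loss rate continued for a second 6 months (an assumption the article does not make), retention would be 0.85 x 0.85 = 0.7225, about 72%. Then 160 x 0.7225 = 115.6, about 58 per arm, with 76.1% power at d = 0.50.

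**The case against.** The division itself cannot be disputed, but several points limit what may be built on it.

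- **64 per arm may carry more than 80%.** The goal is worded as a minimum. If 64 per arm gave 83%, 60 would still give about 80.5%; if 85%, about 82.6%. This stands as a limit on the power figure. It does not reconcile the numbers, because the section presents 64 as what adequate power required.
- **The ANCOVA may recover the loss.** Adjustment for a baseline value with correlation r to the outcome divides the needed number by 1 / (1 - r^2). For 60 to do the work of 64, r^2 = 1 - 60/64 = 0.0625, so r = 0.25. That may well be met, but the article states no correlation and does not say whether the 64 already includes adjustment. Claiming the gain could count it twice.
- **Multiple imputation keeps everyone in the analysis.** Imputation does not by itself restore the information lost with missing 12-month outcomes, and the Sample Size section itself allows for losses.
- **A journal article condenses.** That excuses omissions. Here three stated figures contradict one another.

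A reader might infer more than the text supports in two places. One is that 160 was really built on 80% retention. No section mentions 80%, and 128 x 1.25 fits equally well and sits better with the 75% given twice. The other is that describing 75% as conservative is refuted by the pilot. The 75% lies below the only observed figure, 85%; the 72% needs a constant loss rate; the two differ by under 3 points; and the Limitations section already warns that death or nursing home placement may lower retention.

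**Conclusion.** The inconsistency is real and rests on the article's figures alone: 128 completers at 75% retention need 171 or 172 enrolled, and 160 enrolled at 75% leaves 60 per arm against a stated need of 64.

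The consequence for power is conditional. Under a two-sided 5% t test and an effect for which 64 per arm gives about 80%, unadjusted power at 60 per arm is about 77.5%, a loss of 2 to 3 points. It would be too strong to say that the trial certainly falls below 80%: the effect size and alpha are not given, baseline adjustment may help, and retention of 80% or better would deliver the 128. What can be said is that the stated power does not follow from the stated assumptions. The estimand, the analysis and the conduct of the trial are unaffected.

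**What to change.** Correct the Sample Size paragraph before the analysis begins:

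1. Keep the 75% retention assumption and state that 160 enrolled is expected to leave about 120 participants, 60 per arm.
2. Replace the claim of 80% power or more with the power at 60 per arm (about 77 to 78% unadjusted on the assumptions above), and state the effect size and alpha that produce it.
3. Claim credit for baseline adjustment only with a stated baseline to 12-month correlation, and only if the 64 does not already include it.

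Relabelling 160 as resting on 80% retention would make the division work, but it would replace an assumption recorded twice with a more optimistic one after 159 participants were enrolled, and is not advised. The 75% under Limitations and Potential Challenges can stand; it would help to note there that the pilot's 85% covers only half of this trial's follow-up.

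The cost is a text correction and a slightly less favourable power statement. No extra enrolment or design change is needed.

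### Enrolling 160 at the stated 75% retention gives about 120 completers, not the 128 behind the 80% power claim, and 75% is not a conservative figure

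*Protocol article*

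**What the plan says.** The Sample Size section gives the aim: "The sample size was determined to achieve at least 80% power to detect group differences on both primary outcomes: care partner burden and BPSD". It gives the number needed: "Adequate power required 64 participants per group (or N=128 in total) based on previous work [16]". It then moves from that number to the enrolment target: "Conservatively estimating 75% retention, a target total of 160 was set". Setting and Participants splits the target equally: "There will be 80 participants in the intervention arm and 80 in the attention control comparator".

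The basis of the retention figure appears only in Limitations and Potential Challenges: "Sample size was calculated assuming a 75% participant retention rate, as the 6-month pilot had 85% of participants complete the study". The same paragraph warns that "the likelihood of care recipient death or nursing home placement increases with the duration of the study" and that retention may therefore fall short of what was expected. Study Design sets the follow-up: "Participants will remain in the study for 12 months". The Introduction gives the pilot's size as 53 care partners.

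**The concern.** Retention is the only link between the 128 participants that the power statement needs and the 160 to be enrolled. Two things are wrong with that link.

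First, the three numbers 128, 75% and 160 are mutually inconsistent. At the stated retention, the target falls short of the stated requirement.

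Second, the retention figure is called conservative, yet its stated support is a completion rate over half of this trial's follow-up. A conservative figure should lie below what the supporting evidence projects for 12 months. This one lies slightly above a plain projection.

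What is at stake is how the result is read. A reader of the Sample Size section will believe that 80% power is protected against attrition with some margin. On the protocol's own figures it is not, and a null result could be given more weight than the design supports.

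**Working it through.** **Inputs from the protocol article**
- Required: 64 per group, 128 in total, for at least 80% power (Sample Size).
- Retention 75%, enrolment 160 (Sample Size); 80 per arm (Setting and Participants).
- Pilot: 85% completion over 6 months (Limitations); 53 care partners (Introduction).
- Follow-up in this trial: 12 months (Study Design).

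**Assumptions, because the article does not state them**
- Two-sided 5% test. The Analyses section uses 2-sided 95% CIs and 2-tailed P values, but no design alpha is given with the sample size.
- Standardized difference d = 0.5. No effect size is given. A two-sample t-test with d = 0.5 and 80% power needs 63.8 per group, rounded up to 64, so this reproduces the plan's figure. Power at 64 per group is 80.1%.

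**Step 1. Inflation for attrition**
- Enrolment needed = completers needed / retention = 128 / 0.75 = 170.7, so 171.
- Completers delivered by 160 at 75%: 160 × 0.75 = 120, or 60 per arm.
- Retention at which 160 gives 128: 128 / 160 = 80%.
- 160 also equals 128 × 1.25, which adds 25% to the requirement instead of dividing by 0.75. The article does not say how 160 was reached.

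**Step 2. The retention figure over 12 months**
- If the pilot's 6-month attrition repeats in the second half-year: 0.85 × 0.85 = 72.25%.
- For 75% to hold after 85% at 6 months, the second half-year must keep 0.75 / 0.85 = 88.2% of those left.
- For the 80% that 160 needs, it must keep 0.80 / 0.85 = 94.1%.
- Completers at 72.25%: 160 × 0.7225 = 115.6, about 58 per arm. Keeping 128 would need 128 / 0.7225 = 177.2, so 178 enrolled.

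**Step 3. Power (t-test, d = 0.5, two-sided 5%)**

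| Retention | Completers from 160 | Per arm | Power |
|---|---|---|---|
| 80% | 128 | 64 | 80.1% |
| 75% (stated) | 120 | 60 | 77.5% |
| 72.25% (pilot rate repeated) | 115.6 | about 58 | about 76% |

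**Step 4. Which cause does what**
- Shortfall at the stated 75%: 128 − 120 = 8 completers and 80.1 − 77.5 = 2.6 power points.
- Further shortfall from 75% to 72.25%: 120 − 115.6 = 4.4 completers and, at 58 per arm (76.1%), 77.5 − 76.1 = 1.4 power points.
- Of the 12.4 missing completers in total, 8 (about two thirds) come from the inconsistent inflation.

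**The case against.** **The 72% is only a projection.** It assumes equal attrition in both half-years, and the article gives no 12-month rate. The authors did not carry 85% over unchanged but planned 10 points lower. The pilot was also small: if 45 of 53 completed (inferred from 85%), the Wilson 95% interval is about 73% to 92%, or about 53% to 85% when squared, so 75% is well inside it. This stands, and it means that 75% is plausible. It does not make 75% conservative. Step 1 does not depend on it at all.

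**The risk is already disclosed.** The Limitations section says that retention may fall short. True, but it attaches no number, and it does not touch the mismatch between 128, 75% and 160.

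**The planned analysis may recover precision.** It uses ANCOVA adjusted for baseline, with multiple imputation, whereas the check uses an unadjusted t-test on completers. This stands: the power figures are approximate. The Sample Size section, however, claims no such credit; it ties power to a participant count and a retention rate.

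**Stronger readings that the article does not support**
- *The pilot extrapolation causes the whole fall from 80% to 76%.* Step 4 shows that it causes the smaller part.
- *Death and nursing home placement push retention below 72%.* The article says that their likelihood rises with study duration. Cumulative risk does so even at a constant rate, and squaring 0.85 already extends the pilot's losses to a second half-year. Nothing says that the rate accelerates.
- *The interim count of 42 completers among 159 enrolled shows poor retention.* Enrolment dates are not given, so the number who had reached 12 months is unknown. If 56 had, 42 would be exactly 75%. The count carries no weight either way.

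**Conclusion.** The point holds. On the protocol's own inputs, 160 enrolled at 75% retention yields about 120 completers, 8 fewer than the 128 on which the power statement rests. Power is then about 77.5% rather than at least 80%. The completer shortfall is plain arithmetic; the power figure rests on the assumed t-test with d = 0.5.

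The word *conservatively* is also unsupported, because a 6-month rate is used for a 12-month trial. Under constant attrition the expectation is about 116 completers and about 76% power, a modest further loss. This part is a judgement about an input and does not show that 75% is wrong.

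The total loss, about 4 power points, does not undermine the trial. It does make a stated design property inaccurate, and that is cheap to correct.

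**What to change.** In Sample Size, keep 75% as the assumption actually used at design and delete the word *conservatively*. Replacing 75% with 72% would misreport the design history and leave 160 even harder to explain. Then add a statement along these lines:

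> With 160 enrolled, 75% retention gives about 120 completers (60 per arm) and about 77.5% power for the effect that 64 per group detects with 80% power. If the pilot's 6-month attrition repeats in the second half-year, about 116 completers (58 per arm) and about 76% power are expected. These figures are approximate, because the planned analysis is baseline-adjusted and uses multiple imputation.

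The effect size and alpha behind 64 per group should be stated alongside, in place of the values assumed here. Observed 12-month retention, pooled over arms (completers divided by participants past their 12-month date), may replace the pilot projection and needs no unblinding.

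Align the retention sentence in Limitations and Potential Challenges, saying that 85% is a 6-month figure and what it implies at 12 months.

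The cost is a few sentences and one recalculation, and the stated power becomes slightly less favourable. With 159 of 160 already enrolled by March 2025 (Results), no change to enrolment is proposed.
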